### Data Collection and Management

We have designed a standardized case report form (CRF) for data collection. The CRF comprises the following sections: (1) demographic data, including age, gender, and educational level; (2) vital signs and physical examination, including blood pressure, pulse, height, and weight; (3) medical history, including past medical history, comorbidities, family history, and allergy history; (4) lifestyle habits (tobacco smoking and alcohol consumption); (5) AD assessments from baseline to week 52, including EASI, BSA, IGA, DLQI, NRS, POEM, ADCT, and TCM symptom scale; and (6) previous and current medications and AEs.

The aforementioned information will be collected by well-trained and experienced assessors through face-to-face interviews and subsequently documented in the CRFs. All CRFs will be verified by specialized personnel to preserve the integrity and accuracy of the information. CRF data will be uploaded to the National Clinical Research Center for Skin and Immune Diseases Real-World Big Data Collection Platform. Medical records will be retained at each study site in both paper and electronic formats. All data will be anonymized by removing any personally identifiable information that could directly reveal participant identities.

### Statistical Analysis

This study will use the SAS software (version 9.4; SAS Institute) for statistical analysis. The reasons for missing data will be analyzed, and the multiple imputation method will be used for data completion. Statistical description and analysis will be performed on demographic characteristics and efficacy evaluation data. Quantitative variables following a normal distribution will be described using means and SDs and analyzed using either the 2-tailed *t* test or 2-tailed paired *t* test. Skew-distributed quantitative variables will be summarized as medians and IQRs and analyzed using the Wilcoxon rank-sum test. The quantitative variables of repeated measurement will be analyzed via repeated-measure ANOVA. Qualitative variables will be expressed as frequencies and percentages. The comparison between groups for categorical data will be conducted using the chi-square test, whereas repeated-measurement categorical data will be analyzed using the generalized estimating equations method. Generalized estimating equations models will be fitted with achievement of EASI75 response at each visit as the dependent variable and treatment regimen as the independent variable, adjusted for demographic characteristics (age and sex), medical history (family history and comorbidities), baseline disease severity (EASI, BSA, and IGA), and lifestyle factors (smoking and drinking). The working correlation structure will be selected based on the minimum quasi-likelihood under the independence model criterion. In addition, subgroup analyses will be performed stratified by age, sex, and disease severity. In this study, a *P* value below .05 will be considered statistically significant.

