## Methods

### Study Design

This is a multicenter, prospective, real-world study that will be conducted at 28 hospitals participating in the National Clinical Research Center for Skin and Immune Diseases Real-World Big Data Collection Platform from October 2024 to September 2028. The hospitals are listed in Table S1 in Multimedia Appendix 1. On the basis of the “disease-syndrome” classification framework, patients will be assigned to 7 groups according to their specific clinical presentations (n=500 per group): heat accumulation in the heart and spleen pattern (group A), heart fire with spleen deficiency pattern (group B), spleen deficiency with dampness pattern (group C), wind heat and dampness pattern (group D), spleen deficiency with blood dryness pattern (group E), spleen and kidney yang deficiency pattern (group F), and other patterns (group G). Patients in all groups will undergo a 16-week treatment phase and then a 36-week follow-up period. Baseline is defined as the time of enrollment (week 0) prior to the initiation of any treatment. Assessments will be conducted at baseline, every 2 weeks until week 16, and then every 4 weeks until week 52. The flowchart of this study is shown in Figure 1.

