### Treatment Plan

The treatment plans of patients included in the study are formulated in accordance with the expert consensus on TCM diagnosis and treatment of AD [22] and the guidelines for diagnosis and treatment of AD in TCM [21]. Patients in groups A to F will receive both TCM and biologic treatment (TCMIB groups), whereas patients in group G will receive biologic treatment only. TCM prescriptions include Sanxin Daochi decoction, Peitu Qingxin decoction, Xiao’er Huashi decoction, Shenling Baizhu powder, Xiaofeng powder, Jianpi Runfu decoction, Zhenwu decoction, and Wuling powder. All TCM prescriptions are administered as decoctions for oral use. The standard dosage is 1 dose per day, which is decocted in water and divided into 2 warm servings of 200 mL each. Dermatologists are permitted to individualize the base prescriptions according to each patient’s specific pattern differentiation. The biologic agent used in this study is dupilumab. The dosing regimen follows the expert consensus for dupilumab in the treatment of AD [10]: an initial dose of 600 mg (administered as two 300-mg subcutaneous injections) with a maintenance dose of 300 mg subcutaneously every 2 weeks. Patients in all 7 groups will undergo a 16-week treatment phase and then a 36-week follow-up period. Detailed treatment regimens are provided in Table S2 in Multimedia Appendix 1.

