This protocol outlines the design of a prospective, multicenter, large-scale observational study that provides a real-world setting to explore the role of TCM in the diagnosis and treatment of, constitutional regulation of, and prevention of relapse in AD. To our knowledge, this is the first multicenter observational study in China to enroll at least 3500 patients with moderate to severe AD. The study will analyze the demographic and TCM-specific characteristic profiles of the AD cohort and identify optimal TCMIB therapeutic strategies through long-term observation. Furthermore, it will provide critical data on the effectiveness and safety of a 16-week TCMIB intervention and explore whether this treatment yields additional clinical benefits. Beyond these immediate goals, the creation of a shared clinical database is expected to provide substantial data support for subsequent TCM research, ultimately contributing to the progression of AD clinical research and management.

There are some limitations to this study. First, patient-reported outcomes such as NRS for pruritus and POEM are inherently subjective and may be biased by interindividual differences in symptom perception thresholds. Second, the total period of this study is 52 weeks (including a 16-week treatment period and a 36-week follow-up period). For various reasons, some patients may have difficulty completing the whole study cycle, resulting in loss to follow-up. Third, as this is a real-world study, patients’ treatment regimens are not randomly assigned, making the results susceptible to certain biases. The potential influence of unmeasured confounding factors on the study results cannot be excluded, which poses challenges to causal inference. Fourth, while external TCM treatment methods (eg, topical Chinese medicine and acupuncture) have all shown therapeutic promise in AD [33-35], this study is restricted to oral TCM formulations. This focus limits the comprehensiveness of the assessment regarding the full therapeutic potential of TCM for AD.

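### The quantitative secondary outcomes are compared without covariate adjustment in non-randomised groups, and the text does not say which analysis decides EASI75 at week 16

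*Protocol article*

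**What the plan says.** **How groups arise.** Study Design: "patients will be assigned to 7 groups according to their specific clinical presentations". The groups are TCM patterns, and group G collects all other patterns. Under Treatment Plan, groups A to F receive TCM plus dupilumab, "whereas patients in group G will receive biologic treatment only". The limitations (Discussion, Expected Findings) concede that "patients’ treatment regimens are not randomly assigned, making the results susceptible to certain biases".

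**How quantitative outcomes are analysed.** Statistical Analysis gives three routes:
- Normally distributed variables are "analyzed using either the 2-tailed *t* test or 2-tailed paired *t* test".
- Skewed variables are "summarized as medians and IQRs and analyzed using the Wilcoxon rank-sum test".
- For repeated measurements: "The quantitative variables of repeated measurement will be analyzed via repeated-measure ANOVA".

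No covariate is attached to any of the three.

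**How categorical outcomes are analysed.** "The comparison between groups for categorical data will be conducted using the chi-square test", while repeated categorical data go to GEE. One GEE is then spelled out. It models EASI75 at each visit on treatment regimen, adjusted for age, sex, family history, comorbidities, baseline EASI, BSA and IGA, smoking and drinking.

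**The concern.** Treatment follows group, and group follows clinical presentation. Patients with and without TCM may therefore differ at baseline in ways that affect outcome. The plan accepts this for EASI75, which gets a full covariate list, but attaches none of those covariates to the six quantitative scales that make up most of the secondary outcomes. Any measured imbalance would then appear in those results as if it were a treatment difference, and the study is large enough for a small imbalance to reach significance.

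A second gap concerns the primary outcome. EASI75 at week 16 fits the description of both the chi-square comparison and the adjusted GEE. The two can disagree, and no sentence says which one the conclusion rests on.

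**Working it through.** **1. The plan's own figure.** Sample Size gives 57% versus 70%, two-sided alpha .01, power 90% and 15% dropout. The stated formula gives (2.576 + 1.282)² × (0.57 × 0.43 + 0.70 × 0.30) / 0.13² = 400.7, so 401 evaluable patients, and 401 / 0.85 = 472 per group. This matches the article. The figure is not in dispute; it serves only to fix the scale. With 500 enrolled, 500 × 0.85 = 425 are evaluable per group, and 6 × 425 = 2550 in groups A to F together.

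**2. Which outcomes lack adjustment.**
- EASI score, BSA, DLQI, pruritus NRS, POEM and ADCT are quantitative, so they go to the t test, rank-sum test or repeated-measures ANOVA with no covariates named.
- IGA is an ordinal 0 to 5 scale and the TCM symptom scale is described as nonquantitative. If both are treated as repeated categorical data they go to GEE, with covariates unstated.
- EASI75 at each visit goes to GEE with covariates stated. Visits are every 2 weeks to week 16, so week 16 is included.

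**3. Size of the bias on the EASI score.** The documents give no baseline data by pattern, so both inputs are assumptions: a baseline gap D of 2 to 4 points and a slope b of week-16 EASI on baseline of 0.3 to 0.7. With no true effect:
- raw week-16 difference: bias = b × D
- change from baseline: bias = (b − 1) × D

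| b | D | Raw week 16 | Change from baseline |
|---|---|---|---|
| 0.3 | 2 | +0.6 | −1.4 |
| 0.3 | 4 | +1.2 | −2.8 |
| 0.7 | 2 | +1.4 | −0.6 |
| 0.7 | 4 | +2.8 | −1.2 |

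Both contrasts are off by 0.6 to 2.8 points, in opposite directions. Which one applies depends on whether the ANOVA takes baseline as one of its time points, and the article does not say.

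**4. What a small bias does at this sample size.** Take a bias of d SD, no true effect and a two-sided test at .05. The standard error in SD units is √(1/425 + 1/n₂), and the rejection rate is 1 − Φ(1.96 − d/SE) + Φ(−1.96 − d/SE).
- One group against G (n₂ = 425, SE = 0.069): d = 0.05, 0.10, 0.20 gives 11%, 31%, 83%.
- Groups A to F pooled against G (n₂ = 2550, SE = 0.052): 16%, 48%, 97%.

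The values of d are illustrative.

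**The case against.** **A condensed article need not list every covariate.** For repeated-measures ANOVA the article is silent on covariates and does not exclude them; a fuller document could add them. This is fair for the ANOVA, and for sphericity corrections, on which nothing here relies. It does not cover the other two routes: an ordinary t test and a rank-sum test have no place for covariates. Nor does it explain why the same paragraph lists covariates in full for one outcome and none for six others.

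**The primary outcome is already adjusted.** This stands. A reader might infer that the week-16 EASI75 comparison is purely unadjusted. The text does not support that, because the GEE covers each visit. The sentence that assigns repeated categorical data to GEE even suggests that GEE is the intended route. What remains is that the deciding analysis is not named.

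**Not every secondary outcome is affected.** This also stands. A reader might infer that all secondary outcomes are compared without adjustment. Repeated categorical data go to GEE, so for IGA and the TCM symptom scale adjustment is unstated, not excluded.

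**The size is assumed.** This is correct. Nothing in the documents shows that the groups will differ at baseline, or by how much. The figures show sensitivity and are not a forecast.

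**Confounding is already acknowledged.** The limitations do mention it, particularly unmeasured confounding. That does not justify leaving measured confounders out of the analysis when they are being collected.

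**Conclusion.** The point holds for the six quantitative secondary outcomes and for the unnamed primary analysis. As written, the plan compares EASI score, BSA, DLQI, pruritus NRS, POEM and ADCT between non-randomised groups by methods with no covariates, although it specifies suitable covariates for EASI75. Under the assumed inputs the EASI comparison would be off by 0.6 to 2.8 points either way. If the groups turn out balanced, the bias is nil. The defect is moderate and worth correcting: the primary outcome has an adjusted model, and the remedy is cheap.

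A reader might also infer that adjustment would isolate the effect of adding TCM. The design does not allow this. Only group G goes without TCM, and it is defined by pattern, so treatment and pattern remain tied together whatever covariates are used. Adjustment removes measured baseline imbalance and nothing more.

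**What to change.** - **Quantitative secondary outcomes.** Use a linear mixed model for repeated measures with the outcome's own baseline value, treatment regimen, visit, treatment-by-visit, and the covariates already listed for the EASI75 GEE. The baseline values of DLQI, NRS, POEM and ADCT are not in that list and need to be added for their own models.
- **Primary outcome.** State that the week-16 contrast from the covariate-adjusted EASI75 GEE is the primary analysis, and that the model includes the visit terms needed to give that contrast.
- **Unadjusted tests.** Label between-group t, rank-sum and chi-square tests as descriptive or supportive. Within-group paired tests can stay as description.
- **Limits.** State that adjustment cannot separate treatment from TCM pattern, and word the conclusions to match.

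**Cost.** Changes to the analysis text and modest programming in the SAS version already named. The covariates and baseline scores are on the case report form (Data Collection and Management), so no new data are needed. The article reports 900 patients recruited at submission, out of at least 3500 planned, and analysis starting in June 2028, so the change can still be specified before analysis.

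### Covariate adjustment is stated only for EASI75; the secondary comparisons between non-randomised groups have none stated, so measured baseline differences can bias them in either direction

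*Protocol article*

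**What the plan says.** Groups are not randomised. Under Study Design, "patients will be assigned to 7 groups according to their specific clinical presentations". Under Treatment Plan, "Patients in groups A to F will receive both TCM and biologic treatment (TCMIB groups), whereas patients in group G will receive biologic treatment only". The limitations paragraph under Expected Findings concedes that "patients’ treatment regimens are not randomly assigned, making the results susceptible to certain biases".

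The Statistical Analysis section assigns methods by type of data:

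- Normal quantitative variables: t test or paired t test.
- Skewed quantitative variables: Wilcoxon rank-sum test.
- Repeated quantitative variables: "The quantitative variables of repeated measurement will be analyzed via repeated-measure ANOVA".
- Categorical variables: "The comparison between groups for categorical data will be conducted using the chi-square test".
- Repeated categorical variables: generalized estimating equations (GEE).

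One model is then described with covariates: "Generalized estimating equations models will be fitted with achievement of EASI75 response at each visit as the dependent variable", with regimen as the independent variable. It is adjusted for age, sex, family history, comorbidities, baseline EASI, BSA and IGA, smoking and drinking. No covariates are named for any other outcome. Subgroup analyses by age, sex and disease severity are also planned.

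**The concern.** Groups defined by clinical presentation can be expected to differ at baseline in severity, itch, age and comorbidity. The plan recognises this for EASI75 and adjusts for a sensible list of factors. The same paragraph sends the repeated scores to methods for which no adjustment is stated, and two of these, the t test and the rank-sum test, cannot take covariates at all. Stratified subgroup analyses do not adjust the overall comparison.

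The limitations paragraph names unmeasured confounding as the residual threat. For the secondary outcomes, measured confounding would also stay uncontrolled if the stated methods were followed. These outcomes carry the results on itch, quality of life and disease control. An unadjusted difference on one of them could stand beside an adjusted EASI75 result that points elsewhere, and a reader could not tell how much of the gap comes from baseline differences.

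**Working it through.** **Which outcomes are affected.** The Secondary Outcomes section lists eight.

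| Outcomes | Data type | Method that fits the type | Covariates stated |
|---|---|---|---|
| EASI score, BSA, DLQI, NRS, POEM, ADCT | repeated quantitative | repeated-measures ANOVA; t or rank-sum test at single visits | none |
| IGA, TCM symptom scale | ordinal; nonquantitative | GEE if treated as repeated categorical; chi-square at a single visit | none |

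**The plan's own figure.** The Sample Size section gives 472 per group. Its formula yields (2.576 + 1.282)² × (0.57 × 0.43 + 0.70 × 0.30) / 0.13² = 400.7, rounded up to 401; 401 / 0.85 = 471.8, rounded up to 472. The figure reproduces and is not in dispute. It supplies the 15% dropout rate.

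**Size of the possible bias.**

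From the documents: 500 per group, six TCM groups against one, 15% dropout, P < .05. Evaluable: 500 × 0.85 = 425 in G and 6 × 425 = 2550 in A-F.

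Assumed, not in the documents:
- no true treatment effect
- baseline difference d = 0.1 to 0.3 SD
- baseline to week-16 correlation ρ = 0.3 to 0.5
- equal SDs at both times
- a week-16 value that depends on baseline but not on group

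Formulas, in SD units:
- Week-16 value: bias = ρd; SE = √(1/n₁ + 1/n₂).
- Change from baseline: bias = (1 − ρ)d in absolute size; SE = √(1/n₁ + 1/n₂) × √(2(1 − ρ)), because change has variance 2(1 − ρ).
- Type I error = P(|Z + bias/SE| > 1.96).

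SE for week-16 values: √(1/2550 + 1/425) = 0.0524 for A-F against G; √(2/425) = 0.0686 for one pattern against G. For change, the factor √(2(1 − ρ)) is 1.18 at ρ = 0.3 and 1.00 at ρ = 0.5.

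| d | ρ | Week-16, A-F v G | Week-16, one pattern v G | Change, A-F v G | Change, one pattern v G |
|---|---|---|---|---|---|
| 0.1 | 0.3 | 9% | 7% | 20% | 14% |
| 0.1 | 0.5 | 16% | 11% | 16% | 11% |
| 0.2 | 0.3 | 21% | 14% | 62% | 41% |
| 0.2 | 0.5 | 48% | 31% | 48% | 31% |
| 0.3 | 0.3 | 40% | 26% | 92% | 73% |
| 0.3 | 0.5 | 82% | 59% | 82% | 59% |

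Example, d = 0.3 and ρ = 0.3, A-F against G, change: bias 0.7 × 0.3 = 0.21; SE 0.0524 × 1.18 = 0.0620; ratio 3.39; rejection 92%.

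With d = 0, or with a correctly specified adjustment for that baseline value, the rate is 5%.

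**Direction.** Suppose A-F start worse by d. Their week-16 scores are then worse by ρd, which understates TCM, while their fall from baseline is larger by (1 − ρ)d, which overstates it. If A-F start better, both signs reverse.

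**The case against.** The strongest reply is that a journal article condenses the full plan. It may describe only its primary-outcome model in detail, and nothing in it says covariates are excluded elsewhere. The methods are mapped to data types, not to named secondary outcomes, and the t, rank-sum and chi-square sentences also cover baseline tables, where unadjusted tests are normal. This stands in part: the text does not show that adjustment has been ruled out. But the section is not silent. It assigns methods to these data types and gives covariates for only one of them, so an analyst who follows it as written leaves measured confounding in place.

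A reader might infer more than the documents support:

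- That every comparison other than EASI75 is a t, rank-sum or chi-square test or an ANOVA. The section also gives GEE for repeated categorical data, and IGA and the TCM scale could fall there. Whether the covariates carry over is unstated.
- That baseline values are ignored. If baseline is one of the time levels in the repeated-measures ANOVA, the group-by-time term does use them. It then acts like a comparison of change and leaves regression to the mean, as in the change columns above.
- That the bias must favour TCM. It can go either way.
- That adjustment would isolate the TCM effect. All of A-F receive TCM and G, the other-patterns group, does not. Pattern and treatment are therefore aliased, in the EASI75 model as well.

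It is also fair to say that the primary outcome has an adjusted model and that the article openly concedes non-random assignment and limits on causal inference.

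**Conclusion.** The point holds in this form: no covariate adjustment is stated for any outcome other than EASI75, although the groups are non-randomised and formed by clinical presentation. Measured baseline differences can therefore bias the secondary comparisons in either direction.

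The error rates above illustrate the size; they do not predict it. They rest on the assumed imbalance and correlation, a normal approximation and a single two-group contrast. They do not model the ANOVA itself or the planned multiple imputation. They do show that, with groups this large, a modest imbalance is enough: at 0.2 SD the nominal 5% becomes 21%-48% for week-16 values in the pooled comparison.

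This should be fixed. It is not critical to the trial, because it touches secondary outcomes only.

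**What to change.** In the Statistical Analysis section:

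1. Analyse each secondary score with a longitudinal mixed model, and categorical secondary outcomes with GEE. Include regimen, visit, regimen-by-visit, the baseline value of that outcome and the covariates already listed for EASI75.
2. Read the regimen contrast at week 16.
3. Label unadjusted t, rank-sum and chi-square tests as descriptive.
4. State that adjustment removes only measured confounding and cannot separate the TCM effect from the pattern.

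The cost is wording and slightly more analysis work. Data Collection and Management shows that the case report form already collects these variables, including the outcome scores from baseline, and analysis is not due to start until June 2028. No new data or patients are needed. The downside is that results then depend on the form of the model.

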### Objectives

In this study, we plan to collect clinically relevant data from patients in a real-world setting. The primary objective of this study is to evaluate the efficacy and safety of TCMIB treatment at 16 weeks in patients with moderate to severe AD, and the secondary objective is to analyze data on the involvement of TCM in the diagnosis, treatment, constitutional regulation, and prevention of relapse in AD so as to provide methodological insights to obtain high-quality evidence and inform future in-depth research on AD treatment. The findings are expected to provide further evidence for standardizing TCMIB regimens in the treatment of AD.

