### Outcomes

#### Primary Outcome

The eczema area and severity index (EASI) is one of the most widely used severity scales for assessing AD skin lesions, quantifying the severity of AD based on the area of involvement and the intensity of 4 clinical signs (erythema, edema or papulation, excoriation, and lichenification) in each body region [23]. The EASI score ranges from 0 to 72, with a higher score indicating a more severe disease condition. In this study, achieving an improvement of 75% or more in the EASI at week 16 from baseline (ie, EASI75) is designated as the primary outcome, calculated using the formula [(EASI at baseline – EASI at week *t*)/EASI at baseline] × 100%. The score will be evaluated at baseline, at every visit during the 16-week treatment period, and throughout the 36-week follow-up.

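### The only covariate-adjusted model for EASI75 is written without visit terms, so its treatment odds ratio pools visits and does not estimate the week-16 primary outcome

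*Protocol article*

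**What the plan says.** Three places in the protocol article point to a single time point. Objectives: "The primary objective of this study is to evaluate the efficacy and safety of TCMIB treatment at 16 weeks". Primary Outcome: "achieving an improvement of 75% or more in the EASI at week 16 from baseline (ie, EASI75) is designated as the primary outcome". Sample Size: assumed EASI75 rates of 57% on biologic alone and 70% on TCMIB, both at week 16.

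EASI itself is collected throughout. Study Design: "Assessments will be conducted at baseline, every 2 weeks until week 16, and then every 4 weeks until week 52". Primary Outcome: "The score will be evaluated at baseline, at every visit during the 16-week treatment period, and throughout the 36-week follow-up". The improvement formula there is written for a general week, so EASI75 status exists at every visit.

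Statistical Analysis assigns the chi-square test to between-group categorical comparisons and GEE to repeated categorical data. It then writes the GEE out: "with achievement of EASI75 response at each visit as the dependent variable and treatment regimen as the independent variable". The adjustment list opens "adjusted for demographic characteristics (age and sex), medical history (family history and comorbidities" and continues with baseline EASI, BSA and IGA, smoking and drinking. The working correlation is to be chosen by the quasi-likelihood information criterion. Visit, treatment-by-visit and a week-16 contrast do not appear, and neither analysis is labelled primary.

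**The concern.** With the response at every visit on the left and only regimen and baseline covariates on the right, the model has one treatment parameter to describe all visits. That parameter compares visit-pooled response between regimens, whereas the declared outcome is the comparison at one visit. The two agree only in special cases.

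This matters because the Discussion concedes that regimens are not randomly assigned. Readers will look to the adjusted estimate, and as written it is not an estimate of the primary outcome. A true week-16 difference may come out smaller or larger than it is. A difference confined to follow-up, which is plausible since relapse prevention is among the secondary objectives, can move the pooled coefficient when week 16 shows nothing.

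**Working it through.** **1. The plan's own figure.** Sample Size gives p1 = 0.57, p2 = 0.70, two-sided alpha .01, power 0.90 and 15% dropout.

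n = (2.576 + 1.282)² × (0.57×0.43 + 0.70×0.30) / 0.13² = 400.7, so 401. Then 401 / 0.85 = 471.8, so 472.

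This matches the stated 472 per group. It is a two-proportion calculation at week 16.

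**2. The week-16 target.** OR = (0.70/0.30) / (0.57/0.43) = 1.76, a difference of 13 points.

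**3. Visits that could enter the GEE.** Weeks 2, 4, …, 16 give 8. Weeks 20, 24, …, 52 give 9. Total 17: 7 before week 16, week 16 itself, and 9 after the treatment phase. Statistical Analysis gives no range, so 17 is inferred from the schedule. On a treatment-phase reading it is 8.

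**4. What a treatment-only model estimates.** With complete data, independence working correlation and no covariates, the coefficient is the log odds ratio of visit-averaged response. If S is the sum of a group's response rates over K visits, its pooled odds are S / (K − S).

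**5. Assumed curves.** The article gives none. Let response rise linearly from 0 at baseline to its week-16 value, then move linearly to a week-52 value.
- Rise, weeks 2-16: the mean of week/16 is 0.5625. For 57%, S = 8 × 0.5625 × 0.57 = 2.565. For 70%, S = 3.150.
- Follow-up, weeks 20-52: the mean of (week − 16)/36 is 5/9, so S = 9 × [p16 + (p52 − p16) × 5/9].

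| Assumed course (biologic alone v TCMIB) | S, biologic alone | S, TCMIB | Pooled OR | Week-16 OR |
|---|---|---|---|---|
| A. Week-16 rates maintained | 7.695 | 9.450 | 1.51 | 1.76 |
| B. Both fall to 30% by week 52 | 6.345 | 7.450 | 1.31 | 1.76 |
| C. Fall to 20% v 50% | 5.845 | 8.450 | 1.89 | 1.76 |
| D. As B, but the difference vanishes as soon as treatment stops | 6.345 | 3.150 + 3.780 = 6.930 | 1.16 | 1.76 |
| E. 57% in both at week 16, then 20% v 50% | 5.845 | 7.345 | 1.45 | 1.00 |
| F. Weeks 2-16 only (K = 8) | 2.565 | 3.150 | 1.38 | 1.76 |

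Example, row C: (8.450/8.550) / (5.845/11.155) = 0.988/0.524 = 1.89.

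**6. Check by simulation.** Fitted GEEs without visit terms, 4,000 patients per group, gave 1.47, 1.34, 1.90 and 1.44 for A, B, C and E. Independence and exchangeable working correlation agreed to two decimals. In the same data sets, a model with treatment-by-visit terms gave week-16 odds ratios of 1.66, 1.93, 1.69 and 0.95, which scatter around the targets of 1.76 and 1.00. A separate simulation had biologic alone going from 5% at week 2 to 57% at week 16 and 25% at week 52, with the difference lost when treatment stops. It gave a pooled OR of about 1.15, close to row D.

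**The case against.** The best defence is that this is a condensed article. Visit is not a confounder, so a list of adjustment variables need not mention it, and an unseen analysis plan may add visit terms and contrasts. That is possible. But the article goes beyond a summary: it fixes the outcome, the regressor, each covariate and the rule for the working correlation, and the model so fixed misses the declared endpoint. Reading "with achievement of EASI75 response at each visit as the dependent variable and treatment regimen as the independent variable" as separate models per visit does not fit well either, because choosing a working correlation implies one longitudinal fit.

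Other parts of the defence stand, and they rule out stronger readings that a reader might infer:

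- **That the GEE is the primary analysis, or that week 16 has no test.** The article never gives the GEE that role. The chi-square test can be applied at week 16 and matches the sample-size formula. Its weakness is that it is unadjusted.
- **That the coefficient certainly covers weeks 2-52.** The analysis section states no range.
- **That the pooled effect is always diluted.** Row C exceeds 1.76.
- **That the study loses a particular amount of power.** With 425 per group and latent correlation 0.5 (400 replicates, two-sided .05), power of the pooled model was 46% if the effect vanished when treatment stopped, 63% if it faded over 12 weeks and 96% if it faded slowly to week 52. The curves are assumed. So is the equal split: groups A-F against G would be about 2,550 v 425 after dropout (6 × 500 × 0.85 and 500 × 0.85).

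**Conclusion.** The point holds as a mismatch between estimand and model. As written, the only adjusted EASI75 analysis yields one odds ratio pooled over up to 17 visits (or 8), while the objective, the primary outcome and the sample size all concern week 16. The change of target does not depend on the assumed curves. It remains on the narrower weeks 2-16 reading, where the pooled odds ratio was 1.38 against 1.76.

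Size and direction do depend on the curves. The pooled odds ratio ran from about 1.15 to 1.9 with 57% v 70% at week 16, and was 1.45 with no difference at week 16. These figures are illustrations without covariates or missing data, not predictions.

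The sample size and the data collection are not in question. The matter should be settled before analysis, but it does not invalidate the study.

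**What to change.** Write the model as EASI75 ~ treatment + visit (categorical) + treatment × visit + the listed covariates. Name the adjusted treatment contrast at week 16 as the primary estimate and test, state which visits enter the model, and report the weeks 20-52 contrasts as secondary. A visit main effect alone would not be enough, since it still forces one common odds ratio. An adjusted model fitted to week 16 only is an acceptable alternative. In either case, say what role the chi-square test has.

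Cost: a sentence or two in the analysis section and no new data. With two regimens and 17 visits the model gains 16 visit and 16 interaction parameters (7 and 7 with 8 visits), a small burden with 3,500 patients planned. If very few patients respond at the earliest visits, those terms may be unstable, and the week-16-only model avoids this. Results schedules the start of data analysis for June 2028, so the change can still be made in advance.
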